### Data management and monitoring

We will use RedCap, a secure platform for online surveys and telephone interview data entry. RedCap minimizes data entry errors because survey respondents and interviewers use the interface to directly enter data. All data collection protocols include a form on which research staff members record any problems with the data collection or adverse events. Once data entry is complete, the data is exported to SAS, where all data manipulations are automatically documented in the process of writing SAS code.

### Measures

#### Aim 1: Measures—coalition capacity

This construct is assessed annually and divided into internal team processes and coalition structural characteristics. Internal team processes include cohesion and efficiency. Cohesion (3 items, α = 0.78) measures the extent to which coalition members perceived feelings of unity, group spirit, trust, and belonging within their coalitions. Efficiency (3 items, α = .91) quantifies the work ethic, efficiency, and task focus of the coalition members.

Coalition structural characteristics consist of network composition and collaborative structure. Measures of collaborative structure under investigation are decentralization and multiplexity. Decentralization is a combination of hierarchy, connectedness, average path length, and clustering [55]. Multiplexity is the number of unique types of cooperation or interaction each partner reported with each other partner, among sharing information, personnel, monetary resources, and other cooperation [56]. Network composition measures are sectoral diversity and intersectoral communication. Following our previous research, sectoral diversity is measured using an entropy index whose value increases as the number of sectors increases and the distribution of the coalition’s membership across sectors equalizes [30]. To measure intersectoral communication, respondents name individuals in the coalition to whom they went to for advice about coalition matters. When an individual cites someone from a different sector as a source of advice, that dyad is counted as an intersectoral tie. A coalition’s intersectoral communication is measured as the coalition’s mean intersectoral ties per respondent [30].

#### Aim 2: Measures—EBP implementation

EBP implementation consists of three core facets assessed annually: (a) quantity. (b) quality, and (c) sustainability. EBP quantity is a coalition-level variable computed as the number of youth reached annually by all coalition-supported EBPs. To estimate the total number of youth reached by a particular EBP, we ask the coordinator of the EBP to report the unduplicated number of youth reached annually at each location where the program is being implemented. Thus, EBP quantity represents the sum “reach” achieved by complementary programs implemented by a coalition to address different developmental stages across the prevention spectrum.

EBP quality is a coordinator-reported program-level variable computed as a composite of 7 scales: (a) staff training (6 items, α = .91); (b) staff motivation and competence (5 items, α = .93); (c) fidelity monitoring (11 items, α = .76); (d) evaluation (13 items, α = .81); (e) dosage (2 items); (f) adherence (7 items); and (g) implementation barriers (11 items, α = .81) (21, 26).

EBP sustainability consists of two measures: (1) overall EBP sustainability and (2) sustainability planning. Overall EBP sustainability is a coalition-level variable that is the sum number of years all EBPs are in operation during years 2–4 of the project, including both existing and new EBPs. An EBP will be designated as non-operational when (a) it has no reach or (b) there is an absence of ongoing training or TA in the past 12 months and no funding available to support the program. Sustainability planning is a coordinator-reported program level outcome (12 items, α =.85) [57].

#### Aim 3: Measures—youth substance use

We use measures from the Pennsylvania Youth Survey and Missouri Youth Survey which include items measuring substance use, along with several risk and protective factors [24, 58]. There are 8 key variables under investigation in this study: dichotomized lifetime use and 30-day use of alcohol, tobacco, marijuana, and opioids, respectively [58, 59].

### Power analysis

We used Optimal Design to estimate power for cluster-randomized trials [60]. In this study, youth-level substance use data and program-level implementation data are clustered within coalitions, which is the level of random assignment. Overall, we will have a power of .80 to detect Cohen’s *d* effect size ranges as follows: aim 1, .24 to .37, a small to medium effect, depending on the measure of coalition capacity; aim 2, .31 to .42, a medium effect, depending on the EBP implementation measure; and aim 3, .25, a small effect, for measures of youth substance use.

### Data analytic plan

For aim 1, multi-level longitudinal growth models will be used to test our hypotheses that coalitions assigned to the Coalition Check-Up condition will show improving coalition capacity over time compared to the comparison condition. Our first step entails testing for baseline differences on all measures of coalition capacity between the two experimental conditions. All models will be estimated in MPlus using full information maximum likehood, which has the advantage of being able to estimate missing data [61].

We will model coalition structural characteristics (decentralization, multiplexity, sectoral diversity, intersectoral communication) as coalition-level dependent variables for aim 1. These dependent variables will be predicted by the experimental condition (0=control; 1= Coalition Check-Up), controlling for potential confounders (e.g., coalition model). Once we have multiple waves of data, measurement occasion will be repeated within coalition, and we will utilize growth modeling in our tests of Coalition Check-Up impact on coalition capacity. We will include pretest (i.e., year 0) measures in the model, enabling us to examine change in these characteristics over time between the two groups. Analyses will start by testing unconditional longitudinal models with maximum likelihood estimation in order to find the best functional form, after which we will test our hypotheses [62]. We will identify the trajectory of coalition capacity using model fit indices—including the AIC, BIC, and the −2 Log Likelihood deviance across different types of longitudinal models, including (a) the empty model (i.e., model with only a random intercept), (b) polynomial growth models, (c) polynomial growth models with random slopes, and (d) piecewise models [13, 62]. Once the developmental trajectory of coalition capacity is properly modeled, it will be predicted by experimental condition (0=control; 1= Coalition Check-Up), controlling for potential confounders.

Member experiences of coalition cohesion and efficiency will be modeled at the member level. Coalition member reports here are nested within coalitions. We will estimate a random intercept for the internal team processes in each analytic model. The effect of the Coalition Check-Up is entered at the level of coalition. We will start by testing for baseline differences in coalition capacity between the two conditions. The longitudinal data will add a third level to this model, necessitating use of growth modeling. We will use the same process to test model fit.

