### Coalition recruitment

We will recruit 68 coalitions from community anti-drug coalitions across Pennsylvania and Missouri, USA. This coalition population is similar to other US coalitions, which enhances study generalizability. These coalitions have received funding from a wide variety of sources, and their activity levels have fluctuated with changes in funding levels over time. Coalitions function in rural, suburban, and urban areas, ranging in age from 1 to 30 years old. We connect with these coalitions through the Evidence-based Prevention and Intervention Support (EPIS) group in the Pennsylvania State University’s Prevention Research Center. The EPIS team interfaces with community agencies, schools, and coalitions to provide support to those attempting to integrate prevention research into their practices.

We are using a layered targeted strategy to recruit coalitions, first with email communications from EPIS TA staff. We then introduce the project at coalition regional meetings organized by EPIS, providing time for questions and small group discussion to connect project researchers with coalition members. We then conduct follow-up phone calls and online meetings. The decision to participate rests on each coalition’s leadership team or at times with the full coalition.

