### Randomization

Matched pairs of coalitions will be randomly assigned to the Coalition Check-Up condition or TA as usual. Coalitions will be matched on level of TA availability at baseline (0 = none, 1 = occasional trainings and group TA, 2 = regularly scheduled group TA, 3 = group TA and regularly scheduled one-on-one supervision, 4 = regularly scheduled one-on-one capacity-building TA), years in operation, coalition model employed, population density, US Census poverty rate, and availability of funding. A random number seed will be generated by an external third party using random.org. SAS Proc Surveyselect uses this random number seed to select one of each pair of coalitions recruited into the study as the intervention condition. Data collectors and data analysts will be blind to study condition, with no circumstances under which unblinding is permissible.

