#### Aim 2: Plan of analysis

Using Mplus, we will test the three hypotheses that coalitions receiving the Coalition Check-Up will implement EBPs with greater (1) quantity, (2) quality, and (3) sustainability as compared to the “TA as usual” condition. Prior to hypothesis tests, we will test for baseline differences on each of these dependent variables.

To test aim 2’s first hypothesis, we will model EBP quantity as a coalition-level dependent variable. Once we have three time points of data, we will estimate the developmental trajectory of EBP quantity with growth models—following aim 1 procedures to identify the best functional form of the growth model. Once the developmental trajectory of EBP quantity is properly modeled, it will be predicted by the experimental condition (0=control; 1= Coalition Check-Up) [62].

For the second hypothesis—i.e., programs implemented by coalitions in the Coalition Check-Up condition have superior implementation quality—the unit of analysis is program level, nested within coalition level. Thus, the analytic model will estimate a random intercept. As in the first hypothesis, growth modeling procedures will estimate the developmental trajectory of EBP quality. Experimental condition (0=control; 1= Coalition Check-Up) will be entered at the level of the coalition. Program type (i.e., school-based curriculum, therapist-driven, mentoring, parent curriculum) and program complexity will be covariates at the program level.

For the third hypothesis—i.e., programs implemented by Coalition Check-Up coalitions have superior sustainability—we will test overall EBP sustainability and sustainability planning separately. Coalition Check-Up impact on sustainability planning will be estimated with a multilevel model accounting for the nesting of programs within coalitions. Program-level covariates include program type, program complexity, and baseline EBP longevity. Since overall EBP sustainability is a coalition-level dependent variable, the regression model will not need to adjust for the nesting of programs within coalitions. As with prior models, experimental condition (0=Control; 1= Coalition Check-Up) will be entered at the coalition level.

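### Aim 1 and Aim 2 growth models: the year 0 means are not tied together across randomised arms, which on the ordinary reading gives away precision

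*Protocol article*

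**What the plan says.** Randomization: "Matched pairs of coalitions will be randomly assigned to the Coalition Check-Up condition or TA as usual". Coalition recruitment: "We will recruit 68 coalitions from community anti-drug coalitions across Pennsylvania and Missouri, USA", which gives 34 per arm. The Aim 1 data collection section describes annual surveys for four years.

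The Data analytic plan for Aim 1 first tests for baseline differences between conditions. It then repeats measurement occasion within coalition for the structural measures and adds: "We will include pretest (i.e., year 0) measures in the model, enabling us to examine change in these characteristics over time between the two groups". A functional form is chosen by fit indices, and then: "Once the developmental trajectory of coalition capacity is properly modeled, it will be predicted by experimental condition", controlling for potential confounders. Coalition model is the only confounder named.

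For member-reported cohesion and efficiency, the procedure for judging fit is carried over: "The longitudinal data will add a third level to this model, necessitating use of growth modeling. We will use the same process to test model".

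The Aim 2 plan follows the Aim 1 procedure to find the functional form for EBP quantity, and then: "Once the developmental trajectory of EBP quantity is properly modeled, it will be predicted by the experimental condition". EBP quality is also given a growth model, with condition entered at coalition level.

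Two places do describe baseline covariates. Aim 3 adds a baseline measure as a covariate if the arms differ on it, and the sustainability planning model adjusts for baseline EBP longevity. Neither applies to the Aim 1 outcomes or to EBP quantity and quality.

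**The concern.** A growth trajectory has a starting level and a rate of change. If year 0 is one of the outcome waves and the trajectory is regressed on condition, the usual model lets condition predict both. Each arm then has its own year 0 mean, and the treatment effect is the difference in change.

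Year 0 precedes the Check-Up and allocation is random, so any year 0 gap between arms is chance. A model that estimates this gap freely removes nearly all of it from follow-up, whatever the correlation between waves. A model that sets the expected gap to zero removes only the part that the correlation supports. Both are unbiased under randomisation, and with a correctly specified model the second is never less precise.

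With 68 randomised units, the outcomes that have one value per coalition per wave (decentralization, multiplexity, sectoral diversity, intersectoral communication, EBP quantity) have little precision to spare. What is at stake is a higher chance of missing a real effect.

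**Working it through.** **The plan's own figure.** The Power analysis section gives, at power .80, "aim 1, .24 to .37, a small to medium effect, depending on the measure of coalition capacity". For one coalition-level measurement with no covariate, the detectable difference is (1.96 + 0.84) × √(2/34) = 0.68 SD (0.69 with t on 66 df). For a member-level outcome the variance is multiplied by ICC + (1 − ICC)/m. With 10 to 30 members and ICC 0.05 to 0.20 (assumed), the detectable difference is about 0.19 to 0.36. ICC, cluster size, covariate R² and alpha are not given, so the stated range can be neither reproduced nor refuted. It does not say how the pretest is used.

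**Inputs.** From the protocol: 68 coalitions, 34 per arm, four annual waves taken as t = 0, 1, 2, 3. Assumed: two-sided 0.05, one value per coalition per wave, linear divergence, unit variance, constant between-wave correlation ρ.

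**Variance of the difference in slopes**, in units of 2/34:

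- Year 0 difference free: (1 − ρ)/Σ(t − 1.5)² = (1 − ρ)/5.
- Year 0 difference fixed at zero: 1/(t′V⁻¹t), with t′V⁻¹t = [14 − 36ρ/(1 + 3ρ)]/(1 − ρ).

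At ρ = 0.5 the free variance is 0.5/5 = 0.100. The constrained information is 2 × (14 − 0.2 × 36) = 13.6, so the variance is 1/13.6 = 0.0735. The ratio is 0.735, a 26% reduction.

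**Power.** With 66 df, 80% power needs a noncentrality of 2.843. Dividing by √0.735 gives 3.32, and power 90%. The detectable year-3 difference falls from 3 × 2.843 × √(0.100 × 2/34) = 0.65 SD to 3 × 2.843 × √(0.0735 × 2/34) = 0.56 SD.

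| Assumed ρ | Variance ratio | Power if the free model has 80% |
|---|---|---|
| 0.3 | 0.601 | 95% |
| 0.5 | 0.735 | 90% |
| 0.7 | 0.852 | 86% |
| 0.8 | 0.904 | 84% |
| 0.9 | 0.954 | 82% |

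**Random slopes.** The slope variance is added to both terms. With intercept share 0.5 and slope variance 0.02, the ratio is 0.0935/0.120 = 0.779 and power 89%. With slope variance 0.05 it is 0.1235/0.150 = 0.824 and 87%. With intercept share 0.7 and slope variance 0.02 to 0.10, ratios are 0.889 to 0.944 and power 84% to 82%. The gain over these settings is about 2 to 9 points.

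**Other structures.** If correlation decays by a factor of 0.7 per year, the ratio is 0.666 and 80% becomes 93%. Using 33 df to reflect the pairs leaves the constant-correlation gains unchanged.

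**Weight on the year 0 gap** in the fitted three-year difference at ρ = 0.5: free, 3 × (0 − 1.5)/5 = −0.9; constrained, 3 × (−2.4)/13.6 = −0.53.

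**The case against.** The strongest objection is that the article does not write out the model. It never says that the intercept is regressed on condition, where time zero is placed, or which coefficient is tested. The Aim 1 hypothesis concerns improvement over time, and a model with condition on the slope only would fit the wording. That detail could sit in an analysis plan that is not shown. This stands as a limit on the claim: the free starting level is the ordinary reading, not quoted text. It does not remove the point. The article does describe how the pretest enters and how condition predicts the trajectory, and it spells out baseline covariates elsewhere but not here.

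A reader might infer that the chance year 0 gap is subtracted in full. That is exact only with two waves or a separate mean at each wave. In the four-wave linear model the weight is −0.9, and in the random-intercept-only candidate the gap would be averaged in at one quarter.

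A reader might also take 10 points as the size of the loss. That holds at ρ = 0.5, which the protocol does not give. For a coalition-level outcome with 34 per arm to reach d = .37 or .24 through pretest adjustment alone, 1 − ρ² must equal (0.37/0.68)² or (0.24/0.68)², so ρ is about 0.84 or 0.94, where the gain is only about 1 to 3 points. The article does not tie particular d values to particular measures, so this is suggestive only. If correlations are lower, the gain is larger where power is short: for a 0.37 SD year-3 difference, 35% against about 46% at ρ = 0.5, and 53% against 60% at 0.7.

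Finally, the member-level and program-level sections expressly carry over model selection and growth modelling, not the sentence about the pretest. The calculation covers neither.

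**Conclusion.** The point holds as a free or cheap improvement. As described, the growth models do not use the fact that randomised arms share an expected year 0 mean. If the starting level is left free, the cost is precision in the condition-by-time effect. There is no bias, and nothing in the document is contradicted.

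For coalition-level outcomes, the recoverable power from a base of 80% is about 15 points at ρ = 0.3, 10 at 0.5, 6 at 0.7, 4 at 0.8 and 2 at 0.9. It is smaller with random slopes. These figures rest on the assumed correlation, linear divergence, four waves, 34 per arm and two-sided 0.05. The size for cohesion, efficiency and EBP quality is unknown. The documents do not support saying that the plan definitely regresses the starting level on condition, or that it loses a fixed amount of power.

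**What to change.** State in the Aim 1 Data analytic plan that time is centred at year 0, the arms share a common pretest mean, and condition predicts change after year 0 but not the year 0 level. Say the same for the cohesion and efficiency models and for the Aim 2 growth models of EBP quantity and quality. The alternative that does the same job is to model the follow-up waves with the pretest value as a covariate in every model, whatever the baseline test shows.

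Report the condition effect on change and the implied final-wave difference. Keep the baseline comparison as description. Show the model with a free starting level as a sensitivity analysis.

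The cost is one path omitted in the Mplus code and one sentence of text, with no new data. The small downside is that the model relies on the pretest being unaffected by allocation, so the timing of year 0 measurement relative to allocation should be confirmed for each outcome.

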As a TA model, the Coalition Check-Up requires 84% less TA time compared to the TA used in Communities That Care and PROSPER (4% FTE per coalition vs. 25% FTE). The Coalition Check-Up TA model is a low-intensity yet tailored solution to the tension between TA effectiveness and cost constraints. It is not specific to a particular community coalition model (e.g., PROSPER) or EBP, instead focusing on common dimensions of coalition capacity and program implementation intended to improve youth outcomes [20, 21]. Such a “light touch” intervention would be more easily sustained and is more likely to be adopted to support sustainability on a national scale than existing evidence-based TA models. Additionally, we do not yet know how coalitions can sustain implementation once TA diminishes. Although coalitions may continue to operate, their engagement and activities tend to decline when TA funding ends [22]. After TA loss, some coalitions have seen large declines in recruitment rates and implementation quality for prevention programming [22, 23]. One potential benefit of the Coalition Check-Up is preventing the usual loss of functioning among coalitions as they lose funding for TA. If effective, the Coalition Check-Up will provide lower-cost and thus more sustainable TA to help community coalitions implement EBPs.

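### The growth form is chosen without condition in the model, from candidates that include a no-change model, and nothing keeps the condition-by-time contrast if that model wins

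*Protocol article*

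**What the plan says.** The Data analytic plan states the Aim 1 hypothesis as one of change: coalitions given the Check-Up "will show improving coalition capacity over time compared to the comparison condition". It then sets an order of work.

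1. The form is sought on models without condition: "Analyses will start by testing unconditional longitudinal models with maximum likelihood estimation in order to find the best functional form".
2. The criteria are fit indices: "We will identify the trajectory of coalition capacity using model fit indices—including the AIC, BIC, and the −2 Log Likelihood deviance". The listed candidates start with "a) the empty model (i.e., model with only a random intercept" and go on to polynomial growth, then "c) polynomial growth models with random slopes, and (d) piecewise models". No rule is given for when the indices disagree.
3. Condition enters last: "Once the developmental trajectory of coalition capacity is properly modeled, it will be predicted by experimental condition".

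The same section applies this process to the member-level outcomes, cohesion and efficiency. In Aim 2: Plan of analysis, EBP quantity is modelled "following aim 1 procedures to identify the best functional form of the growth model", and EBP quality takes its growth modelling from that first hypothesis.

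**The concern.** Fitting unconditional growth models first is ordinary practice when it only describes the shape of the trend. Here the step does more: it decides whether time is in the model that condition will predict. The selection sees the data pooled over arms. If one arm falls while the other rises by a similar amount, the pooled mean is flat, and the only trace of the divergence is extra between-coalition slope variance. Fit indices may not pay for that with 68 coalitions.

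If the empty model is selected, there is no slope for condition to predict. Condition can shift only the mean over all waves, including the year 0 measure, which the intervention cannot have affected. That is a weaker test of a different quantity from the stated hypothesis. Which quantity is tested could also vary from outcome to outcome, depending on fit.

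**Working it through.** **Inputs from the protocol.** 68 coalitions in randomised matched pairs, so 34 per arm; 4 annual waves (Aim 1: Data collection); selection by AIC, BIC and deviance; candidates as listed above. The Power analysis gives power .80 for d of .24 to .37 in Aim 1. That figure cannot be rebuilt, because the intraclass correlation, members per coalition and covariate R² are not stated. It is not disputed here and serves only as a scale.

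**Assumptions (not in the protocol).** Total SD 1 before slopes, wave correlation .6, coalition slope SD .1 a year, linear divergence of .2 SD a year, two-sided 5% tests, coalition-level outcome.

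**What the selection step sees.** The pooled slope is the average of the two arm slopes:
- control -.1, Check-Up +.1: (-.1 + .1)/2 = 0
- control -.2, Check-Up 0: -.1
- control +.1, Check-Up +.3: +.2

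The divergence is the same in all three, but the pooled trend is not.

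**What is tested under each outcome of the search (closed form).** Waves are at 0, 1, 2, 3: mean 1.5, sum of squares about the mean 5.
- Slope contrast: variance of a coalition slope = .4/5 + .1² = .09. SE = √(2 × .09/34) = .073. z = .2/.073 = 2.75, so power is about 78%.
- Averaged-level contrast (empty model): expected difference = .2 × 1.5 = .30, half the final-wave difference of .2 × 3 = .60. Variance of a coalition mean = .6 + .4/4 + .1² × 1.5² = .7225. SE = √(2 × .7225/34) = .206. z = .30/.206 = 1.46, so power is about 31%.

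**How often the empty model wins.** Monte Carlo under the assumptions above. Selection is on ML fits without condition (BIC penalty log 68), condition is then added, and power counts whichever test the selected form leaves available.

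| Control / Check-Up, SD a year | Empty chosen, AIC / BIC | Power under the rule, AIC / BIC | Power, slope contrast fixed |
|---|---|---|---|
| -.1 / +.1 | 62% / 91% | 49% / 35% | 76% |
| -.2 / 0 | 5% / 20% | 76% / 67% | 78% |
| +.1 / +.3 | 0% / 0% | 77% / 77% | 77% |

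The top row uses 1,500 runs and three candidates (empty, linear, linear with random slope). The other rows use 400 runs and seven candidates, including quadratic and piecewise forms. With the seven candidates the top-row selection rates are 58% and 90%, so the wider set does not remove the problem. For -.15 / +.05 the power is 59% (AIC) or 45% (BIC), against 75% to 79% for fixed contrasts.

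**At the size of effect the protocol names.** A separate run (300 replicates, seven candidates, intercept correlation .5 or .7, slope SD 0 to .2) set the total final-wave difference at .37. Here only a condition-by-time rejection was counted.
- Arms at ±.185: empty model in 11–72% (AIC) or 46–95% (BIC). Condition-by-time power is .33–.54 if prespecified, .10–.34 (AIC) or .02–.21 (BIC) under the sequence. The averaged-level test has power .10–.17.
- One arm moves .37 alone: empty model in 5–38% (AIC) or 29–67% (BIC).
- One arm moves .80 alone: 0–2% (AIC) or 0–13% (BIC).

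**The case against.** The strongest reply is that the section itself promises growth modelling in the tests of impact and says the pretest is included so that change can be compared between groups. A random-intercept-only model has no growth, so testing in it would contradict those sentences. The empty model may be meant only as the reference for the deviance comparison, and the exact interaction term could sit in an analysis plan not shown. This stands in part: a reader might infer that the protocol says the differential change will go untested, and it does not say so. But it does fix the order, the criteria and the candidate list, and that sequence contains no safeguard.

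Second, random-slope candidates can absorb the divergence. They help, but not enough. With slope SD .2 and arms at ±.1 a year, AIC picks the empty model in 17% of runs (power 60% against 68%), while BIC still does so in 59% (power 45%).

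Third, a reader might infer that the rule fails in the very scenario the trial hopes for. The Background says "One potential benefit of the Coalition Check-Up is preventing the usual loss of functioning among coalitions as they lose funding for TA". That describes decline in one arm and stability in the other, which is the milder one-arm case, and it is tied to losing TA funding. Under Method, both arms keep access to TA as usual and receive annual assessment reports. Offsetting trends are possible, since activity has fluctuated with funding (Coalition recruitment), but they are not predicted.

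Fourth, the simulations treat coalition-level outcomes only. Their figures should not be carried over to cohesion and efficiency, although the same rule applies there.

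**Conclusion.** The point holds as a conditional weakness in a stated rule. When the arms' changes offset, or the divergence is small, the written sequence can select a model without time and leave the stated hypothesis without its own test. Under the assumptions given, power in the offsetting case falls from about 76% to about 49% (AIC) or 35% (BIC). The size depends on the assumed correlation, slope variance and direction of the arms' trends, none of which the protocol gives, and on which index prevails.

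Two wider readings are not supported. The problem does not reach all of Aim 2: overall EBP sustainability is a coalition-level regression on a sum over years, and sustainability planning is a multilevel model with no stated form search. Nor is there a sound case for inflated type I error: the simulated 6.5% against 5.3% rests on 1,500 runs, with a Monte Carlo standard error of about √(.065 × .935/1500) = .6 points, and is too weak to rely on.

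**What to change.** Add a sentence to the Data analytic plan, and refer to it from the Aim 2 plan: for all Aim 1 outcomes and for EBP quantity and quality, time and the condition-by-time contrast stay in the confirmatory model, with a coalition-level random slope or an unstructured wave covariance, whatever form the unconditional fit indices favour. The search may then choose only the shape of the time trend. Say also which index decides when they disagree.

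Wave as a category crossed with condition, with a baseline-adjusted contrast at the final wave, is one acceptable way to do this. It is not required, and growth modelling can stay.

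The cost is plan wording and a few extra parameters. No data collection or sample size changes.
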